##### Work-related variables

Employees will be asked to complete a ten-item questionnaire after the second session each week, to assess their weekly *burnout at work* (i.e., three single-items from the SMBM; see above), *vigor at work* (i.e., three single-items from the SMVM; see above), *basic need satisfaction* versus *frustration at work* (i.e., three single-items from the Needs Satisfaction-Frustration at Work Scale; see above), and *workload* (one single-item “How heavy was your workload today?” used by Thøgersen-Ntoumanis et al., [28]). Scores will be rated using a bipolar visual analogue scale of ten centimeters with two opposing anchors (e.g., “never” vs. “always”; “very light” vs. “very heavy”).

##### Activity-related variables

Participants in the intervention groups will answer an additional eight-item questionnaire using the same bipolar visual analog scale as described above, in order to assess activity-related variables: *affect valence* (one item; “how do you feel after this session”, with the two opposing anchors “very bad” vs. “very good”) and *affect intensity* (one item; “how do you feel after this session”, with the two opposing anchors “low arousal” vs. “high arousal”), from Ekkekakis, Hall, Van Landuyt, and Petruzzello’s work [90]; five single-item measures assessing each of the *psychological recovery experiences* (see above); and the *perceived effort* (one item; “how intense was the effort you made during the last session?”, with the two opposing anchors “very slightly intense” vs. “very intense”).

### Statistical analysis

#### Analyses of Primary and secondary outcomes

Between-arm differences in changes on the primary and secondary outcomes will be analyzed using generalized linear mixed models (GLMM) according to intention-to-treat and per-protocol principles. Intention-to-treat analyses [91] refer to the effect of treatment “as assigned”, meaning that all participants who are randomized to a condition will be included in the analyses, regardless of dropout or missing values. By contrast, per-protocol analyses refer to the effect of treatment “as received”, excluding only participants who have less than 50% compliance to the 20 sessions in the intervention. GLMM has several advantages over repeated measures ANOVA as it considers the hierarchical nature of the data and can accommodate missing data [92]. To distinguish between short- and long-term intervention effects, two separate series of GLMM analyses were performed for each outcome variable. Two time points (pre and post) were used to determine short-term intervention effects and four time points (pre, post, three- and four-month follow-ups) were used to examine long-term intervention effects. Regarding the short-term intervention effects, differences in changes on the outcome variables as a function of the group allocation will be assessed with models including group, time, and group x time interaction as fixed effects. For the group allocation, contrasts analyses [93] will also be carried out to test our hypotheses (H1 – H4) specifically. For that, three contrasts will be computed. The first one will compare the WLC condition with the Theatre condition, PA-TS and PA-NSS conditions (respectively coded as − 0.75, + 0.25, + 0.25, + 0.25) to test whether doing a leisure activity (PA or Theatre conditions) at the workplace leads to a reduction in burnout and an improvement in vigor (H1a, H1b). The second contrast will compare the Theatre condition with the PA-TS and PA-NSS conditions (respectively coded as − 0.667, + 0.333, + 0.333, while WLC will be coded 0) to test whether PA is more effective than theatre condition (H2) in reducing burnout and improving vigor. Finally, the third contrast will compare the PA-TS condition with the PA-NSS condition (respectively coded as − 0.50, + 0.50, while WLC and Theatre conditions will be coded 0) to test whether the positive effect of PA is more pronounced when the instructor uses a need-supportive style (H3). The same analyses will be performed to examine if the effects of the intervention are still effective three months (T12) and six months (T13) after the end of the intervention period. Since there are more than two-time measurements per participant, we will allow random intercepts for participants and random linear slopes for the repeated measurements at the level of participants. These random effects will allow us to estimate each participant’s outcome variables and the rate of change of these outcomes over time. In all analyses we will control for a number of variables that could influence participants’ outcomes. These include job characteristics, and needs satisfaction-frustration at work. Finally, an estimate of the effect size for each outcome will be reported using the conditional pseudo R^2^, which will be computed using the MuMin package of the R software [94].

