### Sample size

Sample size calculations were based on an a priori power analysis based on a previous study carried out on similar primary outcomes in the workplace [37, 66]. This study has reported a positive effect of the PA intervention on the emotional exhaustion component of burnout, with a small effect size (η^2^ = 0.03; f = 0.176). According to this result, we conducted an analysis with G*Power software [70] examining the evolution of burnout and vigor depending on the conditions as inter-individual factors, with an moderate effect size of d = 0.35, a statistical power of 80%, a threshold of significance at *p* < 0.025 considering our two primary outcomes, a correlation of .5 across repeated measures, and a potential dropout rate of 25% for a 10-week program with 4 groups. The results of this analysis recommend recruiting a minimum of 140 participants, 35 per group.

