
#### Analyses of Psychological and Physiological Mechanisms of the PA – Burnout/Vigor Relationship

Multiple mediation modelling will be used to examine the hypotheses that psychological (i.e., detachment, relaxation, mastery, control, relatedness, and positive affects experiences) and physiological (i.e., cardiorespiratory fitness) mechanisms partially or fully mediate the relationships between workplace PA or expressive activity on one hand and burnout and vigor on the other (H5). Two separate models will be generated with burnout and vigor as dependent variables. To handle the categorical independent variable (i.e., the experimental conditions), we will follow Hayes and Preacher’s [95] guidelines for calculating direct and indirect effects using a multicategorical predictor. Specifically, contrast coding will be used to examine the relative effect of workplace intervention (versus WLC), PA (versus Theatre condition) and PA with instructor using a need-supportive style (versus PA-TS) (see above). The scores of the mediating and dependent variables will be analyzed while controlling for the levels of measurement at baseline (i.e., the autoregressive effects). Autoregression allows the value of the variable at a previous time point to be statistical controlled, thereby reducing the likelihood of bias [96]. Bootstrapping procedures will be used to test the statistical significance of indirect effects of the proposed mediating variables [97]. Bootstrapping is a nonparametric resampling procedure for estimating indirect effects using adjusted (asymmetric) confidence intervals. This procedure is very useful in cases of multiple mediations, for which it is interesting to determine not only whether an indirect effect exists, but which mediator(s) contribute(s) significantly to the effect while controlling for other potential mediators. Point estimates and confidence intervals of relative indirect effects (total and specific) will be estimated from 5000 bootstrapped samples and 95% bias-corrected confidence intervals.

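### The pre-post primary model fits a separate baseline mean for each arm, which is valid but gives up as much as a quarter of the precision at the plan's own correlation

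*Protocol article*

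**What the plan says.** The section on analyses of primary and secondary outcomes defines the short-term analysis as follows: "Two time points (pre and post) were used to determine short-term intervention effects". The fixed part is given as "models including group, time, and group x time interaction as fixed effects", and three contrasts among the arms test H1 to H3. The adjustment variables are described thus: "These include job characteristics, and needs satisfaction-frustration at work". The T0 score of the outcome is not named among them, and no common T0 mean is stated.

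Under Recruitment process, burnout and vigor are measured in the first online survey, which decides eligibility. A second survey collects other baseline measures, but not burnout or vigor, and allocation comes after that. The screening scores are therefore the natural T0 values.

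The Sample size section assumes "a correlation of .5 across repeated measures", 25% dropout and a 0.025 threshold "considering our two primary outcomes". The mediation section analyses mediators and outcomes "while controlling for the levels of measurement at baseline".

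**The concern.** With two time points and complete pairs, a model with group, time and their interaction estimates every contrast as a difference in mean change. Any chance difference between arms at T0 then enters the estimate with weight 1. Under randomisation that difference is pure noise. The best linear correction gives it the weight of the regression slope of T11 on T0, which is .5 at the plan's correlation with equal variances.

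At stake is the width of the intervals, and the power, for the tests on the two primary outcomes. The means to recover the precision are already collected. The mediation models condition on the baseline score of the same outcomes, so the idea is not foreign to the plan.

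**Working it through.** **Inputs.** From Sample size: correlation ρ = .5, α = 0.025 per primary outcome, "a statistical power of 80" per cent, "an moderate effect size of d = 0.35", 25% dropout, four groups, 140 recruited (35 per arm). From the primary analysis: two time points, and all randomised participants kept in the mixed model. The documents give no SDs, so any T0/T11 SD ratio below is an assumption.

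**Step 1. The plan's own figure.** Take the repeated-measures ANOVA group × time interaction with k = 4 groups and m = 2 times, and f = d/2 = 0.175 (the source study's f is 0.176).
- Noncentrality: λ = f²·N·m/(1−ρ) = 0.030625 × N × 4. Degrees of freedom: 3 and N − 4.
- 80% power needs N = 111, or 112 when balanced. At N = 112, λ = 13.72 and power is 80.8%.
- 112 × 1.25 = 140. The stated number is reproduced.

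Among the variants tried (two or four time points, α of 0.025 or 0.05, interaction, within or between test, f near 0.175 or 0.35), only this two-time-point interaction at α = 0.025 gave 140. The sample size therefore rests on the change-score test.

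**Step 2. Loss with complete pairs and equal variances** (T11 SD = 1).
- Change score: variance per person 2(1−ρ) = 1.00.
- Common T0 mean or ANCOVA: 1−ρ² = 0.75.
- Ratio (1+ρ)/2 = 0.75, so the loss is (1−ρ)/2 = 25%. The adjusted standard error is √0.75 = 0.866 of the planned one. A generalised least squares check gave the same ratio for all three contrasts.
- At other correlations the loss is 35% (ρ = .3), 20% (.6), 15% (.7) and 10% (.8).

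**Step 3. Loss with dropouts kept in the mixed model** (T0 on 35 per arm, T11 on 26).
- Free T0 means, variance per arm: (1−ρ²)/26 + (1−ρ)²/35 = 0.75/26 + 0.25/35 = 0.02885 + 0.00714 = 0.03599.
- Common T0 mean: 0.75/26 = 0.02885.
- Ratio 0.80, so the loss is about 20%.

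**Step 4. Loss if eligibility narrows the T0 spread.** Entry requires a burnout score of at least 1.79 and a vigor score of at most 5.00. With r = SD(T0)/SD(T11), complete pairs and ρ = .5, the change-score variance is 1 + r² − 2ρr and the adjusted variance stays 0.75.

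| r (assumed) | Change-score variance | Loss |
|---|---|---|
| 1.0 | 1.00 | 25% |
| 0.9 | 0.91 | 18% |
| 0.8 | 0.84 | 11% |
| 0.7 | 0.79 | 5% |

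**Step 5. Omnibus power at f = 0.175, α = 0.025, equal variances.** The adjusted analysis uses λ/0.75.

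| Complete pairs | λ as planned | Power as planned | λ adjusted | Power adjusted |
|---|---|---|---|---|
| 112 | 13.72 | 80.8% | 18.29 | 92.1% |
| 105 (140 × 0.75) | 12.86 | 77.5% | 17.15 | 89.9% |

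The second row leaves out the non-completers. If their T0 scores stay in the mixed model, step 3 puts the planned λ at about 17.15 × 0.80 = 13.72, the same as in the first row, so planned power is then about 81%.

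**The case against.** The strongest reply is that nothing here is wrong. Group, time and interaction is a standard, unbiased model in a randomised trial, it matches the stated interest in differences in change, and the sample size was computed for that same test. All of this stands. The point is one of efficiency.

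A reader might infer that the choice leaves the trial underpowered. The documents do not support that. The 77.5% at 105 complete pairs reflects inflating 112 by a factor of 1.25 rather than dividing by 0.75, and it ignores the partial information from dropouts. With that information kept, the planned power is about 81%.

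A reader might also take 25% as the loss to expect. It is an upper figure at ρ = .5, for complete pairs and equal variances. The plan's own dropout and intention-to-treat rule bring it to about 20%. Selection on the T0 scores could bring it lower still, by an amount the documents do not allow one to fix.

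The contrast with the mediation section is not a contradiction. Those models condition on baseline to obtain autoregressive paths and limit bias, which is another purpose.

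Finally, the adjustment list is worded openly and a fuller analysis plan may exist. That has some weight, but the fixed effects of the primary model are stated outright, and they include the group term that frees the T0 means.

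**Conclusion.** The concern holds as an avoidable loss of precision in the primary analysis, not as bias, error or inadequate sample size. The loss is up to 25% at ρ = .5, about 20% under the assumed dropout with everyone kept in the model, and less if T0 variance is restricted. On the reading that reproduces 140, and with equal variances, adjustment lifts omnibus power from about 77.5% to about 90% on 105 complete pairs.

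This rests on four assumptions: the plan's ρ of .5, T0 burnout and vigor being the pre-randomisation screening scores, the SD ratios shown, and no change in the correlation from the other covariates, for which the documents give no figure. The direction does not depend on the exact values: under randomisation, and apart from a negligible cost in degrees of freedom, the adjusted model is at least as precise.

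One might want to carry the change to every secondary outcome. The text does not support that as it stands. Job satisfaction, work ability and work performance are in the second survey, which the recruitment section places before allocation. Work motivation is in neither survey list, so its timing relative to randomisation is not stated.

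**What to change.** For burnout and vigor, specify the short-term and long-term models with a T0 mean common to all arms: time terms plus contrast × post-baseline time terms, and no group main effect at T0. This keeps every randomised participant who has a T0 score, so the intention-to-treat statement stands, and the three contrasts keep their coding. For the short-term question, modelling T11 with the T0 score of the same outcome as covariate is an acceptable alternative.

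Apply the same form to those secondary outcomes whose T0 value is collected before randomisation, and state when baseline work motivation is collected.

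The cost is one sentence of analysis wording, plus a clause on that timing. No participants or measurements are added, and the stated 140 need not change.

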### PA, expressive activities and burnout/vigor at work

Nordic walking was chosen because while it allows moderate to vigorous energy expenditure [30], it does not require particular physical qualities, or expensive equipment. Moreover, this activity has been identified as efficient in decreasing fatigue states [31] and there are numerous examples of the successful implementation of walking interventions in the work setting (for a review, see [32]). Comparing participants doing Nordic walking with those in the waiting list control condition enables us to test the effect of PA on burnout and vigor compared to the natural development of these affective states during the same period at work. Based on available research, we hypothesize:*Hypothesis 1a:* the PA intervention is effective in reducing burnout and/or improving vigor at work compared to the waiting list control condition.

In addition to the PA condition, we have included an expressive activity condition (Theatre condition) to compare the effects of two leisure activities, with only one requiring high energy expenditure (Nordic walking). Sonnentag and her colleagues recently recommended that future studies should examine whether employees who engage in creative and cultural activities in their free time report a higher level of well-being thereafter, and recover faster and more effectively from work, than other employees [33]. Indeed, some correlational studies [34, 35] showed positive relationships between the frequency of creative and cultural activities during leisure time and recovery experiences and work engagement. As far as we know, no workplace interventions have examined the effectiveness of expressive activities or compared effects of PA and expressive activities on burnout/vigor. While both activities induce psychological mechanisms explaining improvements in work-related well-being (see below), regular PA leads to additional biological adaptations which could contribute to reduced physiological reactions to stressors [36, 37]. The combination of these psychological and physiological benefits in PA could lead to higher effects on burnout/vigor compared to expressive activities. Consequently, we expect that:*Hypothesis 1b:* the Theatre condition intervention is effective in reducing burnout and/or improving vigor at work*Hypothesis 2:* PA is more effective than Theatre condition in reducing burnout and/or improving vigor at work

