
### Physical Activity and Secondary Outcomes

In addition to burnout and vigor, we will assess the consequence of the different conditions on four secondary outcomes, to check whether PA might also have other positive consequences on important job-related variables. First, we will examine the effects of the intervention on *job satisfaction*. This variable refers to a “pleasurable or positive emotional state resulting from the appraisal of one’s job or job experiences” [44]. Thøgersen-Ntoumani et al. [28] showed that participants in a workplace PA program experienced greater levels of enthusiasm and relaxation at work during the afternoon when they carried out PA during lunchtimes compared to the days when they did not. Then, by referring to SDT [45, 46], we will examine the effect of the intervention on the quality of *work motivation*, namely on autonomous (when the professional activities are experienced as emanating from one’s self) or controlled (when they are experienced as emanating from internal or external pressures) motivation. Such motivations are important to study because they are related to a host of cognitive, affective and behavioral consequences such as well-being, job satisfaction, organizational commitment, workaholism, burnout and turnover intentions [47, 48]. We will also investigate the effect of PA intervention on *work ability*. This refers to the “physical, psychological, and social capability of a worker to perform and interact within their work, and the individual’s specific work demands, health conditions, and mental resources” [49]. It has been demonstrated that burned-out people report decreased work ability [50], and an intervention study [37] reported that a six-week physical activity program improved work ability. Finally, we will study the effect of the intervention on the self-reported *work performance*. This variable refers to work-related activities expected of an employee and how well these activities were executed [51]. A few previous studies [52, 53] have reported that more physically active employees reported higher self-rated work productivity, and that a walking program in the workplace over sixteen weeks [54] increased work-performance by the end of the intervention.*Hypothesis 4:* the PA intervention is effective in improving job satisfaction (H4a), autonomous work motivation (H4b), work ability (H4c), and work performance (H4d).

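### One contrast pooling the three activity arms is used to test both H1a (physical activity) and H1b (Theatre), and no named contrast sets either activity alone against the waiting list

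*Protocol article*

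**What the plan says.** The Background (PA, expressive activities and burnout/vigor at work) sets out two hypotheses about two different activities. H1a is that "the PA intervention is effective in reducing burnout and/or improving vigor at work compared to the waiting list control condition". H1b is that "the Theatre condition intervention is effective in reducing burnout and/or improving vigor at work"; the sentence names no comparator. The same section explains how the walking effect is to be isolated: "Comparing participants doing Nordic walking with those in the waiting list control condition enables us to test the effect of PA".

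Under Analyses of Primary and secondary outcomes, the article says "three contrasts will be computed" so as to test the hypotheses specifically:

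- Contrast 1, for H1a and H1b together: "The first one will compare the WLC condition with the Theatre condition, PA-TS and PA-NSS conditions", "respectively coded as − 0.75, + 0.25, + 0.25, + 0.25".
- Contrast 2, for H2: Theatre against the two PA arms, with WLC coded 0.
- Contrast 3, for H3: PA-TS against PA-NSS, with WLC and Theatre coded 0.

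The mediation section reuses this coding: "contrast coding will be used to examine the relative effect of workplace intervention (versus WLC), PA (versus Theatre condition".

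**The concern.** H1a and H1b can be true or false independently of each other. One pooled contrast gives one p-value, which cannot support one hypothesis and reject the other. If walking works and Theatre does nothing, a significant contrast 1 is still booked as evidence for Theatre, and the reverse also holds. When Theatre is inert, pooling also pulls the estimate for walking down by a third and costs power on the trial's first objective. Contrast 2 does not repair this. A null PA–Theatre difference does not show that both work, and a significant one does not show which of them differs from the waiting list.

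**Working it through.** **Inputs.** From Sample size: significance threshold 0.025 per primary outcome (taken here as two-sided), correlation 0.5 between repeated measures, d = 0.35, 25% dropout, 140 participants, 35 per group. The effects of 0.5 and 0.8 SD are assumptions, added to show a range. Reading 0.35 as an arm-versus-WLC difference in change, in SD units, is also an assumption.

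**The plan's own figure.** Take a group-by-time interaction with 4 groups, 2 time points and f = 0.35/2 = 0.175. The noncentrality is N·f²·2/(1 − 0.5). At N = 112 this is 112 × 0.030625 × 4 = 13.72, and power is 81%; at N = 108 it is 79%. Then 112 × 1.25 = 140, as stated. So 112 completers, or 28 per arm, is the number the plan relies on.

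**What the coefficients estimate.** Inverting the published coding matrix (intercept plus three contrasts; arms in the order WLC, Theatre, PA-TS, PA-NSS) gives these weights on the arm means:

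- C1: (−1, 1/3, 1/3, 1/3)
- C2: (0, −1, 1/2, 1/2)
- C3: (0, 0, −1, 1)

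C1 is therefore (2 × PA effect + Theatre effect)/3. The direct comparisons are combinations of planned coefficients:

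- PA − WLC = C1 + C2/3, weights (−1, 0, 1/2, 1/2)
- Theatre − WLC = C1 − 2·C2/3, weights (−1, 1, 0, 0)

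**Standard errors.** The SD of change is √(2(1 − 0.5)) = 1 outcome SD. With 28 per arm:

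- C1: √(1/28 + 1/84) = 0.218
- PA − WLC: √(1/28 + 1/56) = 0.231
- Theatre − WLC: √(2/28) = 0.267

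**Probability of significance in the beneficial direction**, Φ(effect/SE − 2.241), for one outcome:

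| Truth | Test | 0.35 SD | 0.5 SD | 0.8 SD |
|---|---|---|---|---|
| PA only | C1 (expectation 0.233, 0.333, 0.533) | 12% | 24% | 58% |
| PA only | PA − WLC | 23% | 47% | 89% |
| PA only | Theatre − WLC | 1.25% | 1.25% | 1.25% |
| Theatre only | C1 (expectation 0.117, 0.167, 0.267) | 4% | 7% | 15% |
| Theatre only | PA − WLC | 1.25% | 1.25% | 1.25% |
| All equal | C1 | 26% | 52% | 92% |
| All equal | PA − WLC | 23% | 47% | 89% |
| All equal | Theatre − WLC | 18% | 36% | 77% |

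Worked example, PA only at 0.5 SD: 0.333/0.218 = 1.53, and Φ(1.53 − 2.24) = 0.24.

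**Sensitivity.** A noncentral t calculation with 35 per arm (no dropout) gives 15/29/68% for C1 when only PA works, against 29/56/94% for PA − WLC. With 26 per arm (35 × 0.75, rounded down) these become 11/21.5/53% against 21/43/85%. The pattern does not depend on the arm size chosen.

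**The case against.** The best defence is that contrast 1 does what its description says: it asks whether taking up a leisure activity helps, and for that question it is valid and the most powerful choice. The contrasts are also run in addition to a general group-by-time model, and a condensed article need not list every follow-up test. It is true that nothing in the design or data is lost, since both direct comparisons can be recovered from the planned coefficients. The defence does not cover the assignment of two separate hypotheses to that single contrast, which the article states outright.

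A reader might go further in several directions that the text does not support.

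- **That PA can never be compared with WLC.** The supportable statement is that the comparison is not among the named contrasts.
- **That H4 is tested with the pooled contrast.** H4 claims that "the PA intervention is effective in improving job satisfaction (H4a), autonomous work motivation (H4b" and so on. The analysis section says the contrasts serve H1 to H4 but ties H4 to no particular one.
- **That the mediation analysis credits Theatre's indirect effects to PA.** That section labels contrast 1 as workplace intervention and estimates PA against Theatre separately. What remains is a mismatch: H5 is worded for the PA intervention, while its only comparison with WLC is pooled.
- **That H6a has the same fault.** H6a is worded jointly for PA and Theatre against control, so a pooled contrast is a reasonable match.
- **That false confirmation is frequent in both directions.** At the plan's 0.35 SD it is 12% for H1b and 4% for H1a. The larger figures need larger assumed effects. The error runs mainly from PA to Theatre, because PA carries two thirds of the pooled weight.

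**Conclusion.** The plan is wrong as written for H1a and H1b. Contrast 1 cannot separate them, and following the plan allows one activity's effect to confirm a claim about the other. If only PA works, H1b is wrongly supported in 12/24/58% of trials at 0.35/0.5/0.8 SD, and power for H1a is roughly halved at 0.35 and 0.5 SD. If only Theatre works, H1a is wrongly supported in 4/7/15%.

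The contrast weights follow directly from the published codes. The percentages rest on 28 completers per arm, equal SDs, correlation 0.5, a two-sided 0.025 threshold and a normal approximation. They apply to one outcome. Because the hypotheses are phrased as burnout and/or vigor, the chance of at least one false confirmation across the two outcomes would be somewhat higher. That the waiting list is H1b's comparator is inferred from contrast 1 being the only contrast that includes it.

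**What to change.** In Analyses of Primary and secondary outcomes, for the pre-to-post change:

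- Test H1a with PA against WLC: WLC −1, PA-TS +0.5, PA-NSS +0.5, Theatre 0 (equal to C1 + C2/3).
- Test H1b with Theatre against WLC: WLC −1, Theatre +1, both PA arms 0 (equal to C1 − 2·C2/3), and name WLC as the comparator in the hypothesis.
- Keep contrast 1 only as an any-activity effect, with neither H1a nor H1b attached.
- Use the PA-against-WLC combination wherever a claim concerns the PA intervention against the waiting list. For H4 this means naming the contrast; for H5 it means reporting the indirect effects for that combination.
- Leave H6a as it is.

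The cost is a change of wording, two estimates read from a model already planned, and one more test per outcome. The 0.025 threshold allows only for the two primary outcomes, so the plan should say how the extra test is treated. If all activities are equally effective, power falls from 52% (pooled) to 47% for H1a and 36% for H1b at 0.5 SD, and from 26% to 23% and 18% at 0.35 SD. The loss for H1b is not trivial, but the pooled test gains that power only by not testing Theatre on its own.
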